##### Household and participant registration

For all individuals who have expressed an interest and are, therefore, approached for potential inclusion, the following non-identifiable data will be recorded in secure trial databases: mosque attended; date of birth; gender; smoking status; eligibility criteria; consent given/refused; and reasons for not consenting (if given). The time taken for screening will also be recorded.

All consenting individuals (and households) will be registered in a secure trial database, using their name, date of birth, address, and unique trial ID (both for households and individuals). Only the chief investigator, trial coordinator, and researchers involved in collecting, quality checking and entering data will have access to these identifiable data at any stage of the trial. For the purpose of baseline and follow-up data collection and conducting analyses, only the unique trial ID will be used, thereby ensuring anonymity of data.

Paper consent and agreement to participate forms will be kept in a locked filing cabinet at the ARK Foundation in Dhaka, separate from the rest of the trial data.

#### Baseline assessments

##### Mosque baseline assessment

For each mosque participating in the trial the following information will be recorded at the start of the trial:Catchment areaType of mosque (ethnic and religious denomination)Average estimate of number of people who attend two or more daily prayersAverage estimated size of Friday congregationAverage estimated size of study circle (men)Average estimated size of *Qur’an* classAverage age (self-reported by teacher) of students/children taughtAverage estimated size of study circle (women)

A semi-structured questionnaire will be utilised to measure the pre-intervention training knowledge of the imams/*khatibs* on smoking and SHS exposure.

##### Participant (and household) baseline assessment

Baseline data will be collected from households, and all consenting participants in the household, once informed consent has been provided and before randomisation of their mosque, using questionnaires.

The following data will be collected about the household:Presence of outside space; number of bedrooms; number of residents (adults and children); number of resident smokers (adults and children)Self-reported smoking restrictions, or lack thereof, in the homeNumber of shops that sell tobacco products in neighbourhoodPresence of household amenities (e.g. electricity, flush toilet, etc.)Type of fuel used for cookingPresence of mould/moisture in homes and any damage causedPresence of cattle/pets/poultry in homeMosque attendance

IAQ of the household will also be measured at baseline as 24-h mean levels of PM_2.5_ concentration using the Dylos DC 1700 meter.

The following data will be collected about all consenting participants in the household:Socio-demographic variables (date of birth, gender, education)Self-reported smoking behaviour (≥ 11 years only)St George’s Respiratory Questionnaire (SGRQ) ≥ 11 years; frequency and severity of respiratory symptoms for under 11 year-oldsHealth service useHealth-related quality of life: (EQ-5D-5 L for 18 years and over, Proxy version of the EQ-5D-Y: 1 for 11–17 year olds, PedsQL version 4.0 for under 11 year-olds)Attitudes, social norms, intentions and action planning, self-efficacy, and coping planning with regards to smoking and SHS exposure (≥ 18 years only)

#### Randomisation process

Since the M4bH intervention is an ‘educational’ intervention delivered at a group level, this trial is a cRCT where mosques will be randomly allocated to one of the three trial arms.

Mosque, household and participant recruitment, baseline data collection and randomisation of the 45 participating mosques will be conducted over a period of 6 months. Once recruitment has ceased and mosque and household baseline data collection are complete within a particular mosque, the mosque will be randomly allocated 1:1:1 to one of the three arms using minimisation to ensure balance across the groups on the average estimate size of the Friday prayer congregation (≤ 1500/> 1500) and geographical location (wards within the Mirpur area of Dhaka). Random allocation will be performed by a statistician at the University of York not involved in the recruitment of mosques or households, thus ensuring allocation concealment.

#### Contamination and risk of bias

The process of randomisation will minimise the chance of selection bias. There is a possibility that mosques/or households in the control arms could be exposed to the M4bH intervention. All mosques in the trial area will be identified, including a list of mosques enlisted with the IF. A geographical map of these potential mosques will be prepared and Geographic Information System maps used to ensure that the catchment areas of any two clusters do not overlap. A buffer zone of half a kilometre between mosques will be used to minimise the risk of contamination.

By the nature of the interventions used within this trial, blinding of the participants and the imams and *khatibs* delivering the intervention is not possible. Outcome data collection and data analysis are also not blinded.

In order to minimise loss to follow-up, the household head/lead will be requested to inform the trial team of any relevant changes in the household. FIs will also be in regular contact with the household head/lead over the phone. Households will be informed about follow-up prior to the date. Information materials in the appropriate language will be provided to ensure that participants understand clearly what the expectations would be if they decide and give consent to participate in the trial.

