### Effectiveness and cost-effectiveness evaluation

A pragmatic, three-arm, open-label, cluster randomised controlled trial (cRCT) with concurrent economic evaluation will be conducted over 18 months in 45 mosques and their catchment communities in Mirpur area of Dhaka, Bangladesh. The three trial arms are as follows:Arm 1: M4bH intervention and IAQ feedbackArm 2: M4bH intervention aloneArm 3: Usual services

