**Fig. 2 Fig2:**
[figure not shown]
Indoor Air Quality (IAQ) feedback graph

The second page will have pictorial information about the level of 24-h mean PM_2.5_ concentration of that particular home (with classifications hazardous if PM_2.5_ concentration is > 150 μg/m^3^, unhealthy if 36–150 μg/m^3^, moderate if 12–35 μg/m^3^, and good if < 12 μg/m^3^), information about the adverse effects of SHS exposure, recommendations to reduce SHS exposure in the home, and a target that is achievable by implementing SFH rules within that home. This will be accessible to individuals with a diverse range of literacy and numeracy skills. Trial field investigators (FIs) will deliver and discuss the IAQ feedback with members of the households in person and answer any question raised, which may take approximately 10 min.

Follow-up IAQ measurements will take place at 3 months and 12 months in 30 homes per mosque where high levels of SHS (≥ 35 μg/m^3^) were identified at baseline, plus a small number of households under this threshold if necessary. All followed up homes in all trial arms will receive details of their month-12 IAQ measurements and feedback after trial completion.

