#### Data collection

A total of 16 FIs will screen, recruit households, and collect baseline and follow-up information from 1800 households in 18 months. The FIs will receive 3 days’ training on trial procedures including taking informed consent, administering and completing the questionnaires, delivering IAQ feedback, and ethical issues such as autonomy of households and individual participants on making decisions about participation, freedom to withdraw from the trial without giving any reason or consequence, privacy, confidentiality, anonymity. They will work in pairs during recruitment and baseline data collection for the first few mosques (approximately six mosques) and then work individually with each FI working with one mosque at a time.

Data will be collected using paper-based questionnaires designed specifically for the trial. Collected data will be quality checked and entered into the secure, password-protected database designed specifically for this trial on REDCap (Research Electronic Data Capture), a secure web application for building and managing online surveys and databases (https://projectredcap.org/software/). Collected data will be stored on a central database server.

All data will be stored and transferred following Health Insurance Portability and Accountability Act protocol. The staff involved in the trial will be trained on data protection processes. The staff will be strictly monitored to ensure compliance with privacy standards.

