##### Primary analysis

Twenty-four-hour mean household PM_2.5_ at 3 and 12 months post randomisation will be compared between the groups using a linear covariance-pattern mixed model incorporating the two post randomisation time points and controlling for pertinent baseline covariates at the household and cluster level (including baseline PM_2.5_ value (household-level) and the factors used in the minimisation (cluster-level)). Clustering at the mosque level will be accounted for using a random effect. The correlation of observations within households over time will be modelled by a covariance structure. The mean difference at 12 months will serve as the primary outcome, and the difference at 3 months as a secondary outcome. Residuals will be checked for normality and transformations for the PM_2.5_ data (e.g. log) will be considered. Parameter estimates and corresponding 95% confidence intervals will be presented.

We hypothesise that a combination of the M4bH intervention and IAQ feedback is more effective in improving IAQ than usual services. Therefore, the comparison between the M4bH intervention plus IAQ feedback (arm 1) and usual services (arm 3) will serve as the primary comparison, whilst the comparison between M4bH intervention alone (arm 2) and usual services (arm 3), and between M4bH intervention plus IAQ feedback (arm 1) and M4bH intervention alone (arm 2), will serve as secondary investigations.

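### Outcome collection and analysis are left unblinded with no reason that applies to assessors or analysts, though part of each could be masked at little cost

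*Protocol article*

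**What the plan says.** The trial is declared open-label (Effectiveness and cost-effectiveness evaluation). Under Contamination and risk of bias, the protocol article explains that "blinding of the participants and the imams and *khatibs* delivering the intervention is not possible", because of what the interventions are. The next sentence adds: "Outcome data collection and data analysis are also not blinded". No reason is attached to that second statement.

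Three other sections show who does what:

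- **IAQ feedback intervention:** "Trial field investigators (FIs) will deliver and discuss the IAQ feedback with members of the households in person". This applies to arm 1 only.
- **Data collection:** "A total of 16 FIs will screen, recruit households, and collect baseline and follow-up information from 1800 households in 18 months". The same section says that FIs are trained to administer the questionnaires.
- **Contamination and risk of bias:** "FIs will also be in regular contact with the household head/lead over the phone".

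For the analysis, the Primary analysis section says "Residuals will be checked for normality and transformations for the" PM2.5 data, a log being the example, are to be considered.

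**The concern.** Participants and imams cannot be blinded to a sermon or a feedback leaflet. That does not explain why the person recording an outcome, or the person processing and modelling it, must know the arm. The gap sits in the section meant to deal with bias.

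The self-reported outcomes are the most exposed. Respiratory symptoms, quality of life and smoking restrictions are collected by questionnaire at 3, 6 and 12 months. In arm 1 a household may be answering a member of the team that advised it to change. Quality of life also feeds the QALYs and hence the cost-effectiveness ratios.

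PM2.5 is less exposed, but not closed to influence. Staff choose where the monitor stands, entry and exit times on record sheets are matched to the monitor data before the average is taken, and the analysis scale may be chosen once residuals have been seen. Baseline PM2.5 is measured before randomisation, so adjusting for it cannot remove an arm-related measurement difference that arises at follow-up.

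**Working it through.** **Stated reason against stated practice.** The reason given covers two groups, participants and those who deliver the sermons. The practice covers two more, outcome collectors and analysts. Nothing in the article bridges the two.

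**Inputs, all from the protocol article.** 15 mosques per arm (Recruitment); up to 30 households followed per mosque and 20% attrition at 12 months (Sample size); ICC 0.02, SD 45 μg/m³, target difference 13.5 μg/m³, two-sided 5% level, 90% power (Sample size).

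**Standard error.**

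- Households per mosque at 12 months: 30 × 0.8 = 24. Per arm: 15 × 24 = 360.
- Design effect: 1 + (24 − 1) × 0.02 = 1.46.
- Effective number per arm: 360 / 1.46 = 246.6.
- SE of a difference between two arms: 45 × √(2 / 246.6) = 4.05 μg/m³.

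**The plan's own figure.** 13.5 / 4.05 = 3.33, and Φ(3.33 − 1.96) gives 91.5% power against the stated 90%. The inputs therefore reproduce the plan. Masking changes none of them, so the sample size is not in question.

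**What a measurement bias would do.** If the true effect is zero but follow-up measurement differs systematically by b between two arms, the two-sided rejection rate is Φ(b/SE − 1.96) + Φ(−b/SE − 1.96). For b = 2: b/SE = 0.494, so Φ(−1.466) + Φ(−2.454) = 0.071 + 0.007 = 7.8%. The values of b are assumptions; the documents give none.

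| Assumed bias (μg/m³) | SE 4.05 (no baseline correlation) | SE 3.24 (pre-post correlation 0.6) |
|---|---|---|
| 0 | 5.0% | 5.0% |
| 1 | 5.7% | 6.1% |
| 2 | 7.8% | 9.5% |
| 3 | 11.5% | 15.2% |
| 5 | 23.5% | 33.8% |

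The second column uses the correlation that the plan assumes for arm 1 against arm 2: 45 × √(1 − 0.6²) = 36, and 36 × √(2 / 246.6) = 3.24. A bias of 2 is 2 / 13.5 = 15% of the target difference.

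**Staffing.** 45 mosques over 16 FIs is about 2.8 mosques each, so a different existing FI for a follow-up visit is plausible. Imams and khatibs, not FIs, deliver the sermons, so an FI new to a mosque need not have been told its allocation.

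**The case against.** The case on the other side is substantial.

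- **The primary outcome is automatic.** The monitor logs every minute, and one placement rule applies at every visit in every arm. Inconsistent placement mainly adds noise; bias needs staff to shift it in the same direction by arm. This stands, and is why the self-reported outcomes come first here.
- **Analyst freedom is limited.** The model form, time point, primary comparison and main covariates are fixed, no interim analysis is planned, and an independent Trial Steering Committee reviewed a detailed SAP before outcome collection was complete. That SAP is not shown and may hold a transformation rule. This narrows the point. It does not alter the article's statements that analysis is unblinded and that the scale is considered after a residual check.
- **Field masking cannot be complete.** Under Mechanisms of impact, a questionnaire for the two intervention arms only is part of the month-3 follow-up. Receipt of the programme is also recorded, FIs phone household leads, and participants know their arm. This stands.

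A reader might go further and infer any of the following, which the documents do not support:

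- **The same FI gives feedback in a home and later measures it.** The overlap is shown for the group, not for individuals. The words "then work individually with each FI working with one mosque at a time" follow a clause about working in pairs at recruitment and baseline, and do not establish who does follow-up.
- **Existing staff could fully mask outcome collection.** The month-3 questionnaire alone prevents this for a combined visit.
- **The lack of blinding was a deliberate choice to avoid masking.** The text states the fact and no motive.
- **The allocating statistician also analyses the data.** The article does not say who does the analysis.

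**Conclusion.** The point holds in a limited form. The article commits to unblinded outcome collection and analysis and gives no reason that reaches assessors or analysts. The staff group that delivers arm 1 feedback also collects follow-up data, including the self-reported outcomes. This is a stated design choice, not detail left to another document. It is also not an internal contradiction, since an open-label trial may declare it openly.

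The size of any bias is unknown. The rise from 5% to about 8% rests on an assumed 2 μg/m³ and on the plan's own ICC, SD and attrition. It shows how sensitive the test is and is not evidence that such a bias exists. Nor does it show how much masking would remove; participants' own reaction to being monitored would remain. The case for change is that part of the exposure is avoidable at low cost.

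**What to change.** Replace the sentence with three rules.

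1. Convert, clean and exclude monitor files by household ID, without the arm.
2. Settle exclusions, the residual check and any transformation for the primary model on coded arms. Release the key only once those decisions are signed off. The complier average causal effect and process analyses are exempt, since they cannot be masked.
3. Where feasible, assign follow-up visits, above all month 12, to an existing FI who did not deliver feedback in that mosque. Use the same rota in all three arms, so that a change of FI does not itself mark arm 1. At month 3, give the intervention-only process questionnaire after the outcome measures.

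If rule 3 cannot be met, state why.

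Rules 1 and 2 need only a coded dataset and a sign-off. Rule 3 needs a rota and no extra staff. It costs some continuity between FI and household, and masking will be partial because participants may disclose their arm. Recruitment was still under way when the article was written (Trial status), so the month-12 visits could still be arranged this way.

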#### Withdrawal

Households and participants will be free to withdraw consent and leave the trial at any time without giving a reason. Written information on who to contact if they wish to withdraw will be provided to all participants. They will be able to withdraw by letting any member of the research team know if they wish to do so. If a household or participant withdraws consent to participate, no further data will be collected from them. However, data collected up to the point of withdrawal will be retained and used in the analysis, except where withdrawal of consent for the use of this data is explicit, in which case all data will be destroyed.

#### Sample size

Baseline air particulate data were considered for the households recruited from the first six MCLASS II study mosques to be randomised into the trial. Of the 240 recruited, 222 households had at least 22 h of PM_2.5_ concentration measurement at baseline, with an average PM_2.5_ of 66.5 μg/m^3^. The United States (US) Environmental Protection Agency (EPS) considers an Air Quality Index (AQI) of 101 (equivalent to 35 μg/m^3^) or more to indicate unhealthy levels of air pollutants for sensitive groups such as children and the elderly (https://airnow.gov/index.cfm?action=aqibasics.aqi) [28]. Eighty percent of the 222 households at baseline had an average 24 h PM_2.5_ of 35 or more; among these households the mean (standard deviation; SD) was 75.9 (44.2) μg/m^3^.

We propose to recruit 45 clusters (mosques) and 40 households with at least one resident smoker per cluster, and shall follow up up to 30 households per mosque with average baseline PM_2.5_ of 35 μg/m^3^ or more. If there are more than 30 households in the mosque with average baseline PM_2.5_ of 35 μg/m^3^ or more, then 30 will be randomly selected for PM_2.5_ follow-up at 3 months, with randomly selected reserves for those households that are lost to follow-up at this time. If there are less than 30 households in the mosque with average baseline PM_2.5_ of 35 μg/m^3^ or more, then the shortfall will be made up of randomly selected households with PM_2.5_ under 35 μg/m^3^. The same households followed up at 3 months will be contacted for follow-up again at 12 months. We shall assume a 20% attrition rate at 12 months (the primary time point).

The intracluster correlation coefficient (ICC) for salivary cotinine level was negligible in the MCLASS trial (< 0.01) [19], but we shall assume an ICC of 0.02 in this trial to be conservative. With these figures, we would have 90% power to detect an effect size of 0.3; this is equivalent to a difference of 13.5 (e.g. from 76 μg/m^3^ to 62.5 μg/m^3^) assuming a SD of 45, between each intervention group and the control group, using a two-sided 5% significance level. In practice, we would expect to have greater than 90% power with this sample size by virtue of adjusting the analysis for baseline PM_2.5_ concentrations, which we would expect to be predictive of the follow-up measurement. We have not accounted for this potential pre-post correlation to ensure that the calculation is conservative, and to minimise the risk of the trial being underpowered. In the trial analysis, we may wish to compare the two intervention arms. The difference between these two arms is likely to be much smaller than one we could expect to observe between one of the intervention arms and the control arm. With these figures, we will retain 80% power to detect a smaller effect size of 0.2 between the two intervention groups, assuming a pre-post correlation of 0.6.

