#### Recruitment

We aim to enrol 45 mosques (15 in each arm) and 1800 households (40 from each mosque catchment area) into the trial.

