#### Statistical analysis of effectiveness data

##### Analysis of clinical data

The trial will be analysed and reported according to the Consolidated Standards of Reporting Trials (CONSORT) guidelines extension for cluster trials [38]. A detailed statistical analysis plan has been prepared and reviewed by an independent Trial Steering Committee (TSC) prior to the completion of outcome data collection. All analyses will be conducted following the principles of intention-to-treat (ITT), including all participating households within clusters in the trial arm to which the cluster was randomised, using two-sided statistical tests at the 5% significance level. Summaries of the baseline characteristics of the clusters, households and participants will be presented by trial arm. Continuous measures will be reported using descriptive statistics (e.g. *n*, mean, SD, median, minimum and maximum) and categorical data as counts and percentages. No formal statistical comparisons by trial arm will be undertaken on baseline data.

Screening recruitment, and retention data for mosques and households will be summarised, and a CONSORT flow diagram produced. Reasons for non-eligibility/participation will be reported, where available. Follow-up and withdrawal rates at each time point will be presented by randomised group, with reasons for withdrawals given where available.

All outcome data will be summarised descriptively by randomised group and time point.

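### As written, the month-12 contact list is the set of households seen at month 3, so the primary outcome depends on a post-randomisation response

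*Protocol article*

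**What the plan says.** All references are to the protocol article.

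- **Sample size, selection.** The trial recruits 40 households per mosque and "shall follow up up to 30 households per mosque" with a baseline PM2.5 of 35 μg/m³ or more. Where more than 30 qualify, 30 are drawn at random for month 3, "with randomly selected reserves for those households that are lost to follow-up at this time". Where fewer than 30 qualify, the gap is filled at random from homes below 35. No reserve rule is stated for those mosques.
- **Sample size, month 12.** "The same households followed up at 3 months will be contacted for follow-up again at 12 months". Month 12 is the primary time point, with 20% attrition assumed there.
- **Intervention description; Contamination and risk of bias.** The intervention runs for the first 3 months after randomisation, so the month-3 visit follows exposure. Neither participants nor outcome collection are blinded.
- **Analysis of clinical data.** The analysis follows intention-to-treat principles, "including all participating households within clusters in the trial arm to which the cluster was randomised". Follow-up and withdrawal rates are to be reported by arm at each time point.
- **Primary analysis.** A covariance-pattern mixed model uses months 3 and 12, adjusted for baseline PM2.5.

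**The concern.** Selecting the follow-up subsample on baseline PM2.5 is harmless, because that value precedes randomisation. Making month-12 contact depend on having been seen at month 3 is different. Response at month 3 comes after allocation, in a trial where households know what they have received and arm 1 homes have been given their own air readings. If the kind or number of homes missed at month 3 differs by arm, the arms are no longer comparable in the set that carries the primary outcome.

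The analysis cannot repair this. A household missed at month 3 and not approached at month 12 has no outcome at either time, so it adds nothing to the mixed model beyond its baseline. The same household measured only at month 12 would contribute fully to the primary contrast. Choosing reserves at random does not help, because the homes they replace are not lost at random.

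**Working it through.** **1. The plan's own power figure.** Inputs from Recruitment and Sample size: 15 mosques per arm, 30 households per mosque, 20% attrition, ICC 0.02, difference 13.5, SD 45, two-sided 5%.

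- Households per mosque at month 12: 30 × 0.8 = 24, or 15 × 24 = 360 per arm.
- Design effect: 1 + (24 − 1) × 0.02 = 1.46. Effective n: 360 / 1.46 = 246.6 per arm.
- Standard error of the difference: 45 × √(2 / 246.6) = 4.05 μg/m³.
- Power: Φ(13.5 / 4.05 − 1.96) = 91.5%, against the claim that "we would have 90% power to detect an effect size of 0.3".
- For an effect of 0.2 with pre-post correlation 0.6, the residual SD factor is √(1 − 0.36) = 0.8 and power is 79.3%, against 80% stated.

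Both statements reproduce. The issue is selection, not sample size.

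**2. How many homes the rule touches.** The month-3 loss rate is not given. Assuming 5% to 20%, the number of selected homes missed is 30 × 0.05 = 1.5 to 30 × 0.20 = 6 per mosque, or about 68 to 270 of 45 × 30 = 1350.

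**3. How many reserves exist.** In the first six mosques 222 of 240 homes had valid readings, so 222 / 6 = 37 per mosque, and 80% qualified: 37 × 0.80 = 29.6.

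- Binomial(37, 0.8): probability of 30 or fewer qualifying is 0.63; mean number of reserves is 0.77 per mosque.
- If all 40 homes had valid readings, Binomial(40, 0.8): probability of more than 30 qualifying is 0.73; mean number of reserves is 2.3.

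Both ignore clustering of baseline PM2.5 by mosque. Replacement is therefore limited. The month-12 contact sentence matters more than the reserves, and it applies in every mosque.

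**4. Size of a possible shift.** Let f₁ and f₀ be the shares missed at month 3 in two arms, and δ the amount by which missed homes' month-12 PM2.5 differs from that of homes seen (taken as equal in both arms). The comparison shifts by (f₁ − f₀) × δ in absolute size. The assumed range for δ is 13.5 to 45 μg/m³, or 0.3 to 1 SD.

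- 5-point difference in loss: 0.05 × 13.5 = 0.7; 0.05 × 22.5 = 1.1; 0.05 × 45 = 2.25 μg/m³.
- 10-point difference: 0.10 × 13.5 = 1.35; 0.10 × 22.5 = 2.25; 0.10 × 45 = 4.5 μg/m³.

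The range of 0.7 to 4.5 is 5% to 33% of the 13.5 target. With f₁ = f₀ the shift is zero.

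**5. What re-contact could recover.** Only homes missed at month 3 but obtainable at month 12 are lost because of the rule. If half were obtainable (assumption) and resembled the rest, the removable part would be half of the above, about 0.3 to 2.25 μg/m³. Baseline adjustment would reduce it further, to the extent that baseline predicts δ.

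**6. Power after the change.** If total loss from the original 30 is 20%, power stays at 91.5%. If loss from the original selection is larger (assumption), it is 89.9% with 22 homes per mosque, 87.9% with 20 and 85.3% with 18.

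**The case against.** **The exclusion is implied, not stated.** The same section uses the verb loosely in "shall follow up up to 30 households per mosque", meaning selected for follow-up, so the month-12 sentence may mean only that no new sample is drawn. The IAQ feedback section places both follow-up measurements in 30 homes per mosque chosen on baseline PM2.5, and the Withdrawal section names only withdrawn consent as ending data collection. The article also condenses a fuller protocol. This lowers confidence that missed homes would in fact be skipped. It does not remove the point: no passage in the article provides for trying a missed home again, and the Outcomes section refers back to Sample size for who is followed up.

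Three stronger readings are tempting but not supported.

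- **That the rule contradicts intention-to-treat.** The commitment is to the principles of ITT, with households kept in the arm of their mosque. A planned subsample, or outcomes missing after selection, does not breach that. This is a missing-data problem.
- **That substitution hides attrition.** Analysis of clinical data requires follow-up rates by arm and time point, with reasons where available, and a CONSORT diagram. Reserves are also too few to restore a full 30 in most circumstances.
- **That the rule favours the intervention.** Continuing smokers in arm 1 might avoid the month-3 visit, but control homes, which are offered nothing until the trial ends, might equally disengage. The article gives no basis for either direction, and it plans phone contact and advance notice to limit loss.

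**Conclusion.** The point holds in a limited form and should be fixed. As written, the month-12 list depends on month-3 response, which is post-randomisation and unblinded, and month-12 data that the planned model could use are given up.

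The size is an illustration, because no month-3 loss rate is stated. The shift is about zero if month-3 loss is similar across arms and missed homes differ from the rest by the same amount in each. It is about 0.7 to 4.5 μg/m³, in either direction, for a 5 to 10 point difference in loss and a 13.5 to 45 μg/m³ difference in outcome. Only the part due to homes reachable at month 12 is attributable to the rule.

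A reader might take a larger figure from assuming heavy loss in an intervention arm, none in control, and every missed home reachable later. Nothing in the article supports that combination. Nor does it show a need to draw the follow-up list before randomisation: selection is already random within groups defined by baseline PM2.5.

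**What to change.** Replace the month-12 sentence in Sample size with a rule that every originally selected household is approached at month 12 whatever happened at month 3, unless consent has been withdrawn. Add three consequences:

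- Selected households without a measurement are treated as missing in the mixed model, and those with month 12 only are included.
- Reserves, if kept, enter a sensitivity analysis only.
- Follow-up at each time point is reported against the original selection.

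If re-contact was always intended, the rewording costs nothing more. Otherwise the cost is about 1.5 to 6 extra month-12 contacts per mosque, at an assumed month-3 loss of 5% to 20%. No extra enrolment is needed. The article reports recruitment as still open, so no month-12 visit would yet be affected.
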